### Study organization

The study comprises the participating centres and an organizing board structure that includes a Steering Committee, a Data and Safety Monitoring Board, a Data Coordinating Center, and a Statistical Core Center. Each participating centre has a nominated research assistant to supervise the study and organize local data collection. This study is conducted in compliance with the Helsinki Declaration and an ethical approval was given from the responsible ethical committee of every participating centre.

## Discussion

In most people, a PFO will remain asymptomatic for life. However, since the initial description of a fatal stroke in a young woman linked to a PFO by Cohnheim in 1877, PFO and ASA have been increasingly recognized as potential mediators of several disease manifestations, including paradoxical embolism with the principal risk of cerebral or myocardial infarction, orthostatic desaturation in the setting of the rare platypnoea-orthodeoxia syndrome, refractory hypoxemia due to right-to-left shunt in patients with right ventricular infarction or severe pulmonary disease, neurological decompression illness in divers, migraine with aura, transient global amnesia, obstructive sleep apnea, and high-altitude pulmonary edema.

Several case-control studies using contrast echocardiography showed a strong relation between the presence of PFO and cryptogenic stroke in adults particularly aged <55 years [29-34]. According to a meta-analysis [35], in patients younger than 55 years, a PFO confers a relative risk of 3 (95% CI 2 to 4) comparing ischemic stroke with non-stroke control subjects, and a relative risk of 6 (95% CI 4 to 10) comparing cryptogenic stroke with control subjects with a known cause of stroke.

Medical treatment using antithrombotic drugs, percutaneous device closure, or surgical closure constitute measures for secondary prevention against recurrent embolic events in patients with PFO. To date, published randomized comparisons between these modalities regarding safety and efficacy are lacking.

At present, the most restrictive indications are applied in the USA, where failed medical treatment for secondary stroke prevention constitutes the sole Food and Drug Agency accepted indication for PFO closure with a plea to effect the treatment exclusively in the realm of a randomized study [36].

## Appendix 1: PC-trial endpoints

### Primary composite endpoint

a. Death

1. Fatal stroke: a stroke deemed to have caused death either directly by brain damage or indirectly by some non-neurological complication.

2. Cardiovascular death: including sudden death, myocardial infarction, circulatory failure, pulmonary edema, heart failure and death due to any vascular cause including aortic, mesenteric, or peripheral vascular or embolic disease. An unwitnessed unsuspected death will be counted as sudden death.

3. Non-cardiovascular death: any death not classified as fatal stroke or cardiovascular death.

**b. Nonfatal stroke**: any neurologic deficit lasting for >24 hours.

1. Major stroke: a new neurologic deficit that persists for more than 7 days and increases the NIH Stroke Scale score by >4.

2. Minor stroke: a new neurologic deficit that either resolves completely within 7 days or increased the NIH Stroke Scale score by less than <3.

3. TIA: a transient ischemic attack is defined as a temporary neurologic deficit presumably due to reduced blood flow in a particular cerebral artery lasting for <24 hours with complete resolution of the neurologic deficit.

**c. Peripheral embolism**: any endorgan ischemia other than in the brain caused by reduced blood flow in a particular artery and objectively documented by Duplex, computed tomography (CT), MR imaging, or angiography.

### Secondary endpoints

a. New arrhythmia: any rhythm disorder other than normal sinus rhythm, requiring either hospitalization or pharmacologic or electrical therapy interventions.

b. Myocardial infarction: CK-MB >3 times the upper limit of normal and present in two separate blood samples or new pathological Q-waves in at least two contiguous leads with any elevated CK-MB.

c. Rehospitalization related to PFO or its treatment: >24 hour in-hospital stay, which becomes necessary for the management of complications related either to the PFO or antithrombotic therapy.

d. Device problems (dislodgment, structural failure, infection, thrombosis etc.)

e. Bleeding complications related to antithrombotic therapy will be classified as severe, if requiring any blood transfusion, and minor, if not requiring blood transfusions.

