A residual shunt is not unexpected immediately following device implantation. Subsequent endothelialization occurring over a few months improves the closure rate. Completeness of closure for analysis was therefore assessed by TEE with Valsalva followed by a bubble test at 6 months of follow-up. All patients to be treated with acetylsalicylic acid 100-325 mg/day for 5-6 months following device implantation. Ticlopidine 250-500 mg/day or clopidogrel 75-150 mg/day, could be used complementary or as an alternative in case of intolerance to acetylsalicylic acid. Oral anticoagulation was optional for a period of 6 months, if deemed necessary by the investigator but was discouraged. Provided a satisfactory result of the 6-month contrast TEE, antithrombotic therapy and the recommendation for prophylaxis against endocarditis were discontinued, unless required by another indication.

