### Best medical treatment

Patients randomized to the best medical treatment arm were not undergoing any catheterization procedure but were treated with antithrombotic medication. Since there is no consensus on the most effective medical therapy in preventing recurrent stroke or TIA in patients with PFO and paradoxical embolism, the choice of antithrombotic therapy, either antiplatelet therapy or oral anticoagulation, was left to the discretion of the treating physician. However, all patients randomized to the best medical treatment arm had to be treated with at least one antithrombotic medication. The recommended antithrombotic regimen in this study was oral anticoagulation for a period of 6 months (to be commenced at the time of inclusion in the study), followed by treatment with acetylsalicylic acid 100 mg to 325 mg per day during the remainder of the study. However, alternative treatment regimens using only oral anticoagulation or antiplatelet drugs or a combination of these medications were specifically allowed as considered necessary by the responsible physician. This is in keeping with the goal of the study to compare percutaneous PFO closure against best medical treatment, meaning medical treatment deemed optimal for the individual patient by the responsible physician. The recommended therapeutic range for patients who are orally anticoagulated in this study was an international normalized ratio (INR) of 2.0-3.0. A crossover from oral anticoagulation to antiplatelet therapy with acetylsalicylic acid, ticlopidine, or clopidogrel or vice versa was allowed within the best medical treatment arm. The date of drug therapy change and the reasons was documented in the case record form (CRF). Furthermore, events leading to interruption of antithrombotic therapy or bleeding complications were recorded as adverse events in the follow-up section of the CRF. Medical treatment was commenced immediately after randomization, unless already en route. Any events leading to interruption of antithrombotic therapy as well as any bleeding complications were recorded as adverse events.

The statistical power of this study was based on the population allocated to the best medical treatment group as a whole. Although differences among the different antithrombotic regimens will be analyzed, the statistical power may be inadequate to allow firm respective conclusions.

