### Adverse events

#### Risk of percutaneous PFO closure

The risks of percutaneous PFO closure using the *Amplatzer PFO Occluder *consist of the risk of the implantation procedure and the long-term risk of the device itself. The implantation risks are similar to those of other interventional cardiac procedures [20]. They include complications related to vascular access (1-2%; e.g. bleeding, hematoma, need for transfusion), cardiac perforation with or without tamponade (<1%) [21-26], or air embolism (1-2%). The risks of stroke and myocardial infarction are expected to be lower than with coronary angiography which requires arterial access. The risk of death is minimal.

Complications intrinsic to the PFO device include device embolization (3-6%) primarily into the right circulation. Usually, the device can be retrieved either percutaneously, rarely surgery is needed. Other potential hazards include thrombus formation in the implantation equipment or on the device surface with the risk of subsequent embolization, infective endocarditis, or device collapse due to structural fatigue. Bleeding due to the post implantation medical management is another hazard.

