##### b. Nonprocedural complications

All other adverse events not related to the immediate device implantation period (>24 hours after PFO closure) are considered nonprocedural complications.

- death

- stroke

- peripheral embolism

- need for prolonged hospitalization or readmission

- bleeding complications

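### The definition of the rehospitalization endpoint is narrower than its heading: read literally, it leaves out readmissions caused by the device or its implantation, which arise almost only in the closure arm

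*Protocol article*

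**What the plan says.** Appendix 1 of the protocol article lists five secondary endpoints. Item c has the heading "Rehospitalization related to PFO or its treatment". The definition below it requires an in-hospital stay of more than 24 hours "which becomes necessary for the management of complications related either to the PFO or antithrombotic therapy".

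The neighbouring items deal with treatment harm by type:
- Item d is "Device problems (dislodgment, structural failure, infection, thrombosis etc". It counts the problem, not an admission.
- Item e covers bleeding attributed to drugs: "Bleeding complications related to antithrombotic therapy will be classified as severe" or minor, according to whether transfusion is needed.

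Appendix 4, under the nonprocedural part of the device-related adverse events, lists "need for prolonged hospitalization or readmission". Statistical Methods states that primary and secondary endpoints are analysed with proportional hazards models, by intention to treat.

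**The concern.** In this trial a PFO is treated either by closure or by antithrombotic drugs. The heading of item c covers both. The definition names the condition and the drugs, and omits closure. A patient readmitted for more than 24 hours because of a dislodged or infected device, or an access-site complication, satisfies the heading but not the literal definition.

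At stake is the fairness of one stated between-arm comparison. Readmission for the harms of drug treatment is counted, and readmission for the harms specific to closure is not. A hazard ratio below 1 for rehospitalization could then come partly from the definition rather than from the treatments.

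**Working it through.** The plan gives no expected rate for this endpoint, so there is no figure of its own to reproduce. The sample size of 410 is built on primary-event rates and does not use item c. The check is mainly a comparison of texts.

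**1. Does the PFO, as a named cause, already include the device?** The protocol's own usage suggests not. Item d gives device problems a separate endpoint. The section on the risk of percutaneous closure attributes complications to the implantation and to the device: "Complications intrinsic to the PFO device include device embolization (3-6%) primarily into the right circulation". The definition in item c is an either/or list of two causes, with no residual category.

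**2. In which arm do the omitted admissions fall?** The section Best medical treatment says: "Patients randomized to the best medical treatment arm were not undergoing any catheterization procedure". Study endpoints allows crossover to closure after a primary event, so a few device admissions could occur among patients randomized to medical treatment. Otherwise they belong to the closure arm.

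**3. What is counted in each arm?** Antithrombotic complications count in both. For the closure arm, Implantation procedure says: "All patients to be treated with acetylsalicylic acid 100-325 mg/day for 5-6 months following device implantation". Best medical treatment requires at least one antithrombotic drug and recommends a regimen that runs to the end of the study. With the assumed mean follow-up of 4.5 years (54 months), planned exposure in the medical arm is about 54/6 = 9 to 54/5 = 10.8 times as long. That difference is a genuine feature of the treatments and belongs in the comparison. The difficulty is that the corresponding harm of closure does not enter.

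| Cause of a readmission >24 h | Heading of c | Definition of c | Arm |
|---|---|---|---|
| PFO itself | yes | yes | both |
| Antithrombotic therapy | yes | yes | both, longer exposure in medical arm |
| Device or implantation | yes | not named | almost only closure |

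**4. Direction.** Let C and M be the readmissions counted under the literal definition in the closure and medical arms, and D ≥ 0 the device or implantation readmissions in the closure arm. With arms of equal size and under allocated treatment, the ratio of counts is C/M as defined and (C + D)/M as headed. Since C/M ≤ (C + D)/M, the omission can only lower the closure arm's relative figure.

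**5. Upper limits on size.** Inputs: the complication rates in Risk of percutaneous PFO closure, and 410/2 = 205 closure patients (an assumption of equal allocation).
- Device embolization, 3 to 6%: 205 × 0.03 = 6.2 and 205 × 0.06 = 12.3, so about 6 to 12 patients.
- Vascular access complications, 1 to 2%: 205 × 0.01 = 2.1 and 205 × 0.02 = 4.1, so about 2 to 4 patients.

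With the 414 patients actually enrolled (207 per arm) the rounded counts are the same. These are complications, not readmissions. The document does not say how many would lead to a readmission of more than 24 hours, so D for these two causes lies between 0 and these counts.

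**The case against.** The strongest reply is that the harms are captured elsewhere. Item d counts device problems whether or not the patient is admitted, and Appendix 4 lists readmission among device-related adverse events. This stands as far as it goes: nothing disappears from the trial's safety record. It does not repair item c. Item d is not a count of admissions and has no counterpart in the medical arm. Item e does not name procedural bleeding. The Appendix 4 entry sits under device-related events only, with no matching hospitalization entry under antithrombotic therapy. None of these gives a like-for-like comparison of treatment-related rehospitalization.

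A second reply is that the Clinical Events Committee could apply the heading, or read the PFO as including its closure. It could. The bias would then vanish, but only through an interpretation that the definition does not state.

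A reader might also infer more than the text supports:
- *That no treatment complications of closure patients are counted.* This is wrong. Closure patients take antithrombotic drugs after implantation, and an admission for a resulting bleed qualifies. Only device and implantation complications are in doubt.
- *That a definite number of events is missed.* Adding the complication rates assumes that no patient has two complications. Any fraction converting complications to readmissions would be invented. Many implantation complications will also occur during the index stay and would not be readmissions under any wording.
- *That ignoring a prolonged index stay, or counting an admission for a recurrent stroke here as well as in the primary endpoint, is an error.* A rehospitalization endpoint may reasonably exclude the index stay, and separate endpoints may share an event. These are matters of preference.

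**Conclusion.** The heading and the definition of item c do not agree. Applied literally, the definition leaves device- and implantation-related readmissions out of a between-arm comparison, and under allocated treatment that can only favour closure. This rests on reading the two named causes as a closed list, which the protocol's separate treatment of device and implantation supports but does not make certain.

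The size is unknown. It may be zero, and for the two causes with a stated range it cannot exceed roughly 6 to 12 embolizations and 2 to 4 access complications among an assumed 205 closure patients. The primary endpoint, sample size and significance levels are untouched. The point deserves correction because it is one-directional and cheap to remove, not because it threatens the trial's main conclusion.

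**What to change.** Bring the definition into line with its heading. Item c should count readmissions of more than 24 hours for *complications related to the PFO, the closure procedure, the device or antithrombotic therapy*, with identical wording in both arms. Enrolment is complete and follow-up is continuing, so the clarification should be dated and made before the endpoint is compared by arm, then applied to all events from the start of the trial.

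The cost is small. Implantation complications are already recorded as adverse events, and the Clinical Events Committee already adjudicates all reported adverse events and endpoints, so the work is a change of wording and a reclassification of existing records. The one downside is that the closure-arm figure may be somewhat less favourable.

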#### Risk of medical treatment

The risks of medical treatment relate to adverse events of antithrombotic therapy. Bleeding is the main complication of oral anticoagulant therapy with warfarin or alike [27,28] and is influenced by the intensity of anticoagulation and the concomitant use of antiplatelet agents. The bleeding risk appears higher in patients with a history of prior stroke or gastrointestinal bleeding. Intracranial hemorrhage is estimated to occur with an incidence of 0.5% per year in patients on oral anticoagulant therapy with coumadin. Another important, but uncommon adverse effect of coumadin is skin necrosis. Furthermore many other medications and food components interfere with the metabolism of oral anticoagulants, potentiating or inhibiting their effects.

The principal adverse effects of acetylsalicylic acid are prolonged bleeding due to inhibition of platelet function, stomach irritation, gastritis, or gastrointestinal bleeding. These complications are rare and the therapeutic benefit of acetylsalicylic acid outweighs these potential adverse advents. Acetylsalicylic acid increases the risk for intracranial hemorrhage minimally. In case of intolerance to acetylsalicylic acid, ticlopidine or clopidogrel were used. Adverse event definitions for both treatment modalities are shown in Appendix 4.

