## Appendix 4: Possible adverse events with both treatment modalities

### PFO-device related adverse events

#### Major procedural complications

1. Death occurring within 24 hours of the procedure due to a perioperative complication

2. Cardiac perforation with or without tamponade if requiring pericardiocentesis or surgery

3. Device embolization as dislocation of the PFO device from the atrial septum to another intravascular region necessitating its percutaneous or surgical removal

4. Severe bleeding complication - vascular access site injury requiring surgical correction or significant drop in hemoglobin (>5 g/dl) or requiring transfusion.

5. Intraprocedural stroke (with symptoms persisting for more than 24 hours)

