#### Minor procedural complications

1. Cardiac arrhythmias: sustained cardiac arrhythmias related to device implantation requiring electrical (direct current countershock, pacing) or antiarrhythmic drug therapy. Minor arrhythmias (nonsustained, not requiring treatment) are not considered.

2. Cardiac perforation without need for treatment

3. Vascular access site complications

- local hematoma associated with a palpable mass >4 cm and hemoglobin drop >3 and <5 g/dl.

- arteriovenous fistula

- false aneurysm

4. Air embolism with symptoms persisting for >15 minutes but <24 hours

5. Complications necessitating device removal

6. Transient neurologic deficit (TIA) with complete resolution within 24 hours

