### Adverse events related to antithrombotic therapy

- any event leading to interruption of antithrombotic therapy

- bleeding complications related to antithrombotic therapy

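### Antithrombotic-related bleeding is graded by transfusion alone, so a non-transfused intracranial, fatal or surgically treated bleed is labelled minor, on a different scale from procedural bleeding

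*Protocol article*

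**What the plan says.** Appendix 1 (Secondary endpoints, item e) gives the severity rule for drug-related bleeding: "Bleeding complications related to antithrombotic therapy will be classified as severe, if requiring any blood transfusion, and minor, if not requiring blood transfusions". It has no clause for site, fatal outcome, surgery or fall in haemoglobin.

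The section Risk of medical treatment calls bleeding the main complication of oral anticoagulation and gives a rate for one kind: "Intracranial hemorrhage is estimated to occur with an incidence of 0.5% per year in patients on oral anticoagulant therapy with coumadin".

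Appendix 4 has its own scale for the procedure. Item 4 under Major procedural complications defines a severe bleeding complication as "vascular access site injury requiring surgical correction or significant drop in hemoglobin (>5 g/dl) or requiring transfusion". The minor list includes "local hematoma associated with a palpable mass >4 cm and hemoglobin drop >3 and <5 g/dl". Other items on the major list do not depend on transfusion: item 1 is "Death occurring within 24 hours of the procedure due to a perioperative complication", and item 5 is a stroke during the procedure with symptoms beyond 24 hours.

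The time boundary is set under Nonprocedural complications: "All other adverse events not related to the immediate device implantation period (>24 hours after PFO closure) are considered nonprocedural complications". The last part of Appendix 4 lists "bleeding complications related to antithrombotic therapy" with no severity grade. No section links the two scales.

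**The concern.** A severity label should rank events by seriousness. Item e ranks them by one treatment given. An intracranial bleed managed without blood products, a bleed fatal before any transfusion and a bleed repaired surgically without transfusion all share a grade with trivial bleeding. The article treats intracranial bleeding as serious elsewhere: it names it as a hazard of anticoagulation and excludes patients with a history of it.

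The second problem is comparability. Procedural bleeding, which only the closure arm can have, is judged on wider criteria. Drug-related bleeding occurs in both arms, but the medical arm takes antithrombotic drugs for the rest of the study, while the closure arm is meant to stop after a satisfactory 6-month echocardiogram. The narrow rule therefore weighs mainly on the medical arm. A reader who sets severe procedural bleeds against severe drug-related bleeds would be comparing unlike quantities.

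**Working it through.** The article gives no bleeding figure to reproduce. The check sets the two rules side by side and then sizes the one event for which the article gives a rate.

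**1. The two bleeding rules compared.** Take three features: transfusion, haemoglobin drop above 5 g/dl, and an injury needing surgical correction. That gives 2 × 2 × 2 = 8 combinations.

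| Transfused | Drop >5 g/dl | Surgical correction | Appendix 1, item e | Appendix 4, item 4 |
|---|---|---|---|---|
| no | no | no | minor | not severe |
| no | no | yes | minor | severe |
| no | yes | no | minor | severe |
| no | yes | yes | minor | severe |
| yes | any | any (4 rows) | severe | severe |

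The rules disagree in 3 of 8 combinations. These are all the non-transfused bleeds with a large haemoglobin drop, a surgical correction, or both.

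**2. Fatal and intracranial bleeds.** Under item e, a non-transfused bleed of either kind is minor. Item 4 of Appendix 4 has no fatal or intracranial clause either. In the procedural setting such a bleed would reach the major list through item 1 (death within 24 hours) or item 5 (stroke beyond 24 hours), not through the bleeding item. So the fault for these bleeds lies in item e itself, not in a conflict with item 4.

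**3. Where the scopes meet.** Item e covers bleeding related to antithrombotic therapy; item 4 covers the procedure. The Implantation procedure section has heparin given during closure, and closure patients take antithrombotic drugs afterwards. An access-site bleed in the first 24 hours could be attributed to either cause. After 24 hours it is nonprocedural, a category that lists bleeding without grading it.

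**4. Where the worst bleeds are also counted.** The primary composite in Appendix 1 includes every death. Its nonfatal stroke item covers any neurologic deficit beyond 24 hours, with no restriction to ischaemic causes. Secondary endpoint c covers a hospital stay beyond 24 hours for complications of antithrombotic therapy. All bleeding complications are recorded as adverse events. A nonfatal intracranial bleed without a lasting deficit would escape the primary composite, so its grade under item e matters most.

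**5. Expected number of intracranial bleeds, medical arm.**

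- Rate on oral anticoagulation: 0.005 per year (Risk of medical treatment).
- Patients: 205, which is 410 / 2 (Statistical Methods). Equal allocation is an assumption, since no ratio is stated.
- Exposure: 0.5 years under the recommended regimen (Best medical treatment), or the planned mean follow-up of 4.5 years (Statistical Methods) if every patient stayed anticoagulated throughout.
- Expected count = patients × rate × years. Poisson probability of at least one = 1 − exp(−count).

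| Exposure | Expected count | P(at least one) |
|---|---|---|
| 0.5 years | 205 × 0.005 × 0.5 = 0.51 | 1 − exp(−0.5125) = 0.40 |
| 4.5 years | 205 × 0.005 × 4.5 = 4.6 | 1 − exp(−4.6125) = 0.99 |

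The second row is an upper bound, because it runs against the recommended switch to acetylsalicylic acid at 6 months. The number graded minor is the count times the share not transfused. That share is not in the article and may lie anywhere between 0 and 1.

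**The case against.** The strongest case is that two categories with different scopes may use different criteria without contradiction. This stands in part. A reader might infer that one and the same bleed is routinely graded two ways. The text does not support that: the rules compete only in overlap cases such as an access-site bleed under procedural heparin. What remains is that the two counts are not comparable and that nothing in the article says which rule governs an overlap.

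A reader might also infer that the gravest bleeds vanish from the trial. They do not. Deaths and deficits beyond 24 hours are in the primary composite, long hospital stays are a separate secondary endpoint, and the Clinical Events Committee adjudicates all reported adverse events. Only the severity label is affected. The article gives the committee no other bleeding scale, though, so adjudication does not cure the label.

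Two further inferences fail. Nothing in the article makes severe bleeding its main harm measure; it is the last of five secondary endpoints. Nor is there a basis for saying that bleeding is misstated in both arms: no misgrading of procedural bleeds is shown, and item e applies the same rule to drug-related bleeding in either arm.

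That an article condenses the full protocol does not answer the point. The rule is printed in full and leaves no case open.

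**Conclusion.** The concern holds in limited form. Followed literally, item e labels a non-transfused intracranial, fatal or surgically treated bleed as minor. Its scale also departs from that of Appendix 4 in every non-transfused bleed with surgical correction or a haemoglobin drop above 5 g/dl. The defect is confined to the grade of one secondary safety endpoint and leaves the primary analysis, power and alpha untouched.

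The size is small but not negligible for a safety table: about 0.5 expected intracranial bleeds under recommended anticoagulation, and at most about 4.6 if all medical-arm patients were anticoagulated throughout. These figures rest on the article's own rate, an assumed 205 patients in the arm and the planned mean follow-up. It would be tempting to say that nearly all of these bleeds would be graded minor, but the article does not say how often they are transfused. It also gives no frequency for the other non-transfused bleeds on which the scales differ.

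**What to change.** Reconcile item e of Appendix 1 with item 4 of Appendix 4 in one endpoint severity definition for all bleeding in both arms. Fatal, intracranial and surgically treated bleeds should count as severe alongside transfused ones, and the drop above 5 g/dl already used in Appendix 4 should apply where haemoglobin values are recorded. With one definition, an overlap case gets the same grade whichever category it is filed under.

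Have the Clinical Events Committee regrade the recorded bleeds blind to arm, as far as the records allow, since an access-site bleed reveals the allocation. Report the transfusion-only grade alongside, so that the effect of the change is visible.

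The cost is moderate. Bleeds are already recorded as adverse events, so site, outcome and surgery should be recoverable. Haemoglobin may be incomplete for past bleeds, because Table 1 schedules laboratory work only at baseline and enrolment ended in February 2009. The severe-bleeding rate may come out somewhat higher.
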